### Participant timeline

Every study site will assess patients for eligibility to enroll into the study. Before enrolment, every patient will receive full oral and written information about the nature, purpose, expected advantages and possible risks of the trial. The patient will agree to participate in the trial by signing the informed consent form. Patients, who meet all inclusion criteria, no exclusion criteria and who have given their written informed consent will be randomized for study treatment in one of the two study arms. Eligible patients will be screened up to 10 days prior to randomization. At randomization, patients will be allocated to IMP or placebo. The individual patient will be treated for 10 weeks. The final examination will be performed at visit 8 (week 10). 2 weeks after end-of study a safety follow-up visit will take place. Please see Table 2 for examinations that will be performed at screening and all assessments performed at baseline and the following seven study visits during the trial.

**Table 2 Tab2:** Outline of trial visits

Assessments	SC	BL Visit 1 W 0	Visit 2 W 1	Visit 3 W 2	Visit 4 W 3	Visit 5 W 4	Visit 6 W 6	Visit 7 W 8	Visit 8 W 10	FU Visit 9 W 12
**Screening and consent**										
Inclusion/exclusion criteria	X									
Informed consent	X									
Physical examination^1^	X								X	
Prior and concomitant medi-cation and non-drug therapy	X	X	X	X	X	X	X	X	X	X
Medical history	X									
IMP dispersion		X	X	X	X	X	X	X		
IMP return			X	X	X	X	X	X	X	
**Safety**										
Blood test^2^	X								X	
Cannabis test	X									
Pregnancy test	X	X		X		X	X	X	X	
ECG	X								X	(X)^3^
Blood pressure, pulse	X	X	X	X	X	X	X	X	X	X
Weight	X	X					X		X	X
Adverse event recording		X	X	X	X	X	X	X	X	X
**Effectiveness**										
**Primary**										
CAPS-IV B2									X	
**Secondary**										
CAPS-IV B2	X	X	X	X	X	X	X	X		
CAPS-5	X^a^	X^b^					X^b^		X^b^	
PSQI-A		X					X		X	
MADRS	X	X				X			X	
Sleep diary		X	X	X	X	X	X	X	X	
PCL-5		X					X		X	
BSL-23		X					X		X	
EQ-5D		X					X		X	
PGIC							X		X	
SOFAS		X					X		X	
PSQI		X					X		X	
ITQ		X					X		X	
MWC		X					X		X	X
**Others**										
Demographics	X									
CTQ	X									
MINI-5	X									
ITI	X									

*SC* Screening, *W.* week ± 3 days, *BL* Baseline and randomization, *FU* Post-trial follow-up, *CAPS-IV B2* B2 score of the Clinician-Administered PTSD Scale for DSM-IV (frequency and intensity of nightmares), *CAPS-5* Clinician-Administered PTSD Scale for DSM-5 (a = last month version, b = last week version), *PSQI-A* Pittsburgh Sleep Quality Index-Addendum for PTSD, *MADRS* Montgomery–Åsberg Depression Rating Scale, *PCL-5* PTSD Checklist for DSM-5, *BSL-23* Borderline Symptom List 23, *EQ-5D* Health-Related Quality of Life, *PGIC* Patient Global Impression of Change, *SOFAS* Social and Occupational Functioning Assessment Scale, *PSQI* Pittsburgh Sleep Quality Index, *ITQ* International trauma questionnaire, *MWC* Marijuana Withdrawal Checklist, *CTQ* Childhood trauma questionnaire, *MINI-5* The Mini International Neuropsychiatric Interview for DSM-5, *ITI* International Trauma Interview

^1^Physical examination includes height and weight of the patient and the skin, abdomen, respiratory system, head and extremities will be examined

^2^blood test s include haematology (erythrocytes, haemoglobin, haematocrit, platelets, leukocytes (including neutrophils, eosinophils, basophils, lymphocytes, monocytes) and serum chemistry (sodium, potassium, chloride, calcium, creatinine, alanine aminotransferase, alkaline phosphatase, gamma glutamyl transferase, aspartate aminotransferase, bilirubin, lipase, thyroid stimulating hormone)

^3^In case of significant abnormal ECG findings at the visit 8 (week 10), a further ECG will be recorded at the follow-up visit

### Rational for selection of doses

Due to the experience from previous trials with cannabis-based medication in healthy individuals and clinical groups, including patients with PTSD, the daily dose was determined to be between 2.5 mg per day to 15 mg per day (single administration) with an increase in dose by 2.5 mg every third/fourth day (see Investigators Brochure, Edition Number Final 4.0, Date of release: 30SEP2020, page 30ff, 6. Effects in Humans). The Investigators Brochure recommends 30 mg dronabinol per day as maximal dose. As single dosing will be applied in this study, the maximal daily dose of dronabinol has been restricted to 15 mg which also corresponds to our clinical experience. Effects of THC on nightmares in PTSD have been found in an open label pilot study with 10 mg per day of THC (5 mg twice a day), starting with 5 mg per day (2.5 mg twice a day) [18]. However, pharmacokinetic parameters of dronabinol show high intra-individual variability. To determine the optimal individual dose with respect to efficacy (decrease of intensity and frequency of nightmares) and side effects, up-titration in steps of 2.5 mg dronabinol per day will be performed with an increase every third/fourth day. Alternating increase every third and every fourth day has been chosen to take into account that the clinical visits will take place every seventh day (once a week) in the up-titration period (first four weeks of treatment, Visit 1 to Visit 5).

### Sample size

The sample size calculation is based on the primary endpoint “Clinician-Administered PTSD Scale-IV (CAPS-IV) B2 score at 10 weeks” in the full analysis set including all randomized patients who received the study medication at least once. The aim is to show a lower average score at 10 weeks in the intervention group (I) than in the control group (C). Sample size calculation will be based on a two-sided, two-sample t-test. Adjustment for baseline scores in an ANCOVA model which is applied for the primary efficacy analysis will increase the power compared with a two-sample t-test, which ignores the influence of different baseline values. Therefore, this strategy for sample size calculation is a conservative procedure. In a random-effects meta-analysis of four RCTs investigating the effect of prazosin on PTSD nightmares, a combined standardized mean difference (Cohen’s d) of 0.5 (95% CI = 0.03–0.96) was observed [1]. We conservatively assume a standardized effect which is a little smaller and given by 0.45. This assumed effect can be considered as clinically relevant because distressing nightmares are an independent risk factor for comorbidity and severity in PTSD patients. Nightmares also contribute to alcohol and substance abuse, suicidal ideation, and even completed suicide [17]. As studies assessing minimal clinically important difference (MCID) for reduction of nightmares in PTSD are currently missing, clinical significance cannot be used to calculate sample size.

The required sample size to detect this effect of 0.45 with a power of 0.8 is 158 (79 per group) calculated with nQuery Version 8.2.1.0. We conservatively assume that there will be no more than 10% of patients who are randomized but never get the study medication. Therefore, the total number of patients to be recruited is 176 (158/176 = 0.9) or 88 per group.

### Recruitment

Patients will be recruited via the in- and outpatients center at the recruiting centers. Flyer, advertising the study, will be distributed at other treatment centers and private practice for psychiatry and psychotherapy.

### Randomization and blinding

Patients will be randomized at baseline in a 1:1 allocation using block randomization with fixed block lengths stratified by the study center. Randomization lists are provided by the cooperating pharmacy (Myonex GmbH). Allocation concealment will be ensured, as Myonex GmbH will release the randomisation code after the patient performed baseline assessment (visit 1). Further, block length is unknown to the entire study team. Treatment is blinded by use of a matching placebo. The Sponsor, study personnel, and participants will be blinded to treatment until the database is locked. The investigator is encouraged to maintain the blind as far as possible. In the case of an emergency, access to the study treatment code for an individual subject will be possible at the trial sites. Emergency envelopes containing information to unblind individual participant will be stored at the trial sites. Every trial patient will receive a patient ID card where the address and telephone number of the responsible investigator in case of emergency and the complete address of the trial site will be indicated. The patient ID card contains information that the patient is participating in a clinical trial involving exposure to BX-1 with dronabinol as the active ingredient or corresponding placebo. The decision about necessity of unblinding lies in the responsibility of the investigator or the authorised person.

Staff of all participating study centers will be trained in the study requirements including application of clinical interviews. Clinical interviews will be performed by trained psychologists (master-degree) or medical doctors (in training or with completed training in psychiatry). Training videos of standardized application of CAPS-5, CAPS-IV B2 Item and MADRS will be rated by assessors of the interviews. Raters with divergent ratings will be trained again. Inter-rater-reliability will be calculated for the primary outcome (CAPS-IV B2 Item) after assessment of 10 videos.

The study sites will make maximum effort to follow the participants for the entire study period. We assume that ≈15% of patients (24 participants) who are randomized and received the study medication at least once will not finish the study as planned (“non-completers”). All randomized participants who are prematurely discontinued from the study drug will be considered “off study drug/on study” and will follow the same schedule of events as those participants who continue study treatment.

### Safety

In general, dronabinol is well tolerated, but the patients` individual maximum dose is limited by adverse reactions. Expected adverse reactions are listed in supplementary table S1. Safety assessments include: Blood pressure and heart rate at every visit; assessment of laboratory parameters (safety laboratory) at screening and end of trial (visit 8 in week 10); physical examination at screening and end of trial; ECG at screening, end of trial and in case of significant abnormal ECG findings at visit 8 (week 10) a further ECG at follow-up (visit 9, week 12). Urinary pregnancy test (women only) at screening, baseline, visit 3 (week 2), visit 5 (week 4), visit 6 (week 6), visit 7 (week 8), and visit 8 (week 10). See also Table 2 for an overview of the safety assessments. Standard procedures for reporting of adverse events will be used. Adverse events will be assessed at every visit starting at visit1.

Further safety information and definitions for adverse event (AE), serious AE and Suspected Unexpected Serious Adverse Reactions (SUSAR) are outlined in the online supplemental material.

### Data management

Data collected on each subject will be captured in the medical files (source data) and are consecutively recorded in the eCRF (secuTrial® software). All electronic data will be stored at the server of the Charité Berlin. All essential documents will be kept in the Investigator Site File which will be stored at the study site in accordance with ICH GCP chapter 8.

### Statistical methods – outcome

#### Primary analysis

The aim is to show that the Clinician-Administered PTSD Scale (CAPS-IV) B2 score for the last week at 10 weeks is lower in the intervention group (I) than the control group (C). An ANCOVA model including the baseline score and adjusted for study center will be applied for primary analysis. The global two-sided significance level will be 0.05.

#### Secondary analyses

Descriptive methods will be used to analyse secondary outcomes, including appropriate summary measures of the empirical distribution as well as 95% confidence intervals and descriptive two-sided p-values. For analyses of secondary endpoints considering the primary score at different follow-up times, the same imputation mechanisms as specified below will be applied. For all other secondary endpoints, no imputation is planned.

### Additional analyses

Additionally, sensitivity of the primary analysis will be analysed in different populations to assess the impact of the analysis population and of the imputation method (comparison to per-protocol population, patients with complete cases). All analyses will be done using validated statistical software.

### Analysis population and missing data

Confirmatory analysis will be conducted based on the full analysis set. The full analysis set consists of all randomized patients which received the study medication at least once. Patients are analysed as randomized. This is the population as close as possible to the intention-to-treat population.

The per-protocol population includes all patients without major protocol violations.

Missing values for the analysis of the primary endpoint will be imputed as follows: If the follow-up assessment at 10 weeks is missing but the patient has at least one follow-up assessment after baseline, last-observation-carried-forward will be used for missing value imputation. If the baseline visit is missing but follow-up assessments are available, the baseline value will be imputed using multiple imputation [21].

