### Interventions

Eligible patients will be randomised in equal proportions to dronabinol (BX-1) and placebo, receiving a once-daily oral dose before bedtime for 10 weeks. Of these 10-weeks, the first 4 weeks are considered the titration period, the following 6 weeks are the maintenance period with stable dose.

BX-1 is an oily solution containing 25 mg/ml dronabinol. Dronabinol ((-) trans-Δ9-Tetra-hydrocannabinol, Δ9-THC) is the major psychoactive constituent of Cannabis sativa L.. Dronabinol is a clear to amber resin. It is highly lipid-soluble, thermolabile, photolabile and susceptible to oxidation. There is no discernible difference between BX-1 and the corresponding placebo with regard to color, taste, and appearance, thus ensuring the trial`s double-blind character. BX-1 and placebo are filled in bottles. Study medication (IMP) and placebo will be provided by Bionorica SE, Neumarkt, Germany.

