### Outcomes

#### Primary endpoint

The Clinician-Administered PTSD Scale (CAPS-IV) B2 score measuring frequency and intensity of nightmares for the last week, range 0–8 [3] directly after last intervention (10 weeks).

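### LOCF for a missing week-10 CAPS-IV B2 score can carry a titration-phase rating into the primary endpoint; the resulting bias has no fixed direction, and the planned checks examine it only in part

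*Protocol article*

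**What the plan says.** The primary endpoint is the CAPS-IV B2 score "directly after last intervention (10 weeks"). It is compared in the full analysis set by an ANCOVA with baseline score and study centre (Primary analysis).

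For a missing week-10 score, Analysis population and missing data requires only that "the patient has at least one follow-up assessment after baseline". In that case "last-observation-carried-forward will be used for missing value imputation". No visit is too early to be carried forward. A missing baseline, by contrast, is handled by multiple imputation.

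Under Interventions, "the first 4 weeks are considered the titration period, the following 6 weeks are the maintenance period with stable dose". Titration period allows dose steps up to day 19, and Maintenance period fixes the individual dose at day 28.

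Table 2 schedules B2 in the secondary block as "CAPS-IV B2 X X X X X X X X" (screening, baseline, Visits 2 to 7) and in the primary block at Visit 8. A patient without a Visit 8 score can therefore have up to six post-baseline scores, at weeks 1, 2, 3, 4, 6 and 8.

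Randomization and blinding expects about 15% (24) of patients "who are randomized and received the study medication at least once will not finish the study as planned". It also keeps patients who stop study drug on the same visit schedule. The sensitivity analyses named are a "comparison to per-protocol population, patients with complete cases" (Additional analyses).

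**The concern.** LOCF is correct only if the score would not have changed between the last visit and week 10. This trial is built on the expectation that it will change: the dose is raised over the first weeks and the endpoint is read after a 6-week stable phase. A score from week 1, 2 or 3 does not represent week 10 in either arm.

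Two distortions follow. First, a carried score contains only part of the treatment effect, which dilutes the difference. Second, if patients in both arms improve over time, the arm with more or earlier drop-out looks worse than it is. This second distortion can shrink the effect or inflate it, so LOCF is not reliably conservative. It also treats the filled value as observed, although the intermediate scores that could inform a better prediction are already collected. The confirmatory estimate and p-value are affected. So are the interim efficacy and futility decisions, if the interim uses the same rule.

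**Working it through.** **The plan's own figures.** Inputs from Sample size: d = 0.45, two-sided alpha 0.05, power 0.80. A noncentral-t two-sample calculation gives power 0.7975 at 78 per arm and 0.803 at 79 per arm, so 158 reproduces. 158/0.9 = 175.6, so 176 reproduces. 15% of 158 = 23.7, which is the stated 24. The inflation from 158 to 176 covers patients who never start drug, not those who leave later.

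**Assumptions not in the documents.**
- SD is 1, and both arms improve linearly by c = 1 SD by week 10.
- The treatment effect builds linearly to d = 0.45.
- Missing week-10 shares are mA (active) and mP (placebo), averaging 15%.
- A carried score shows a fraction f of the week-10 change.
- If the last visit is spread evenly over weeks 1 to 4, the mean is 2.5 weeks and f = 0.25. If it is spread evenly over weeks 1, 2, 3, 4, 6 and 8, the mean is 24/6 = 4 weeks and f = 0.40.

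**Expected LOCF difference, active minus placebo.**

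E = −d·[1 − mA(1−f)] + c·(1−f)·(mA − mP)

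The first term is dilution. The second is the drift caused by unequal drop-out.

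With f = 0.25:
- 15%/15%: −0.45 × (1 − 0.1125) = −0.399
- 20%/10%: −0.45 × 0.85 + 0.75 × 0.10 = −0.3825 + 0.075 = −0.308
- 10%/20%: −0.45 × 0.925 − 0.075 = −0.491
- No true effect, 20%/10% and 10%/20%: +0.075 and −0.075

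With f = 0.40:
- 15%/15%: −0.45 × 0.91 = −0.410
- 20%/10%: −0.45 × 0.88 + 0.06 = −0.336
- 10%/20%: −0.45 × 0.94 − 0.06 = −0.483
- No true effect, unequal drop-out: ±0.06

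**Simulated baseline-adjusted ANCOVA.** 79 per arm, correlation 0.6 at 4 weeks, drop-out unrelated to score. The estimates agree with the formula. Rejection rates, each good to about 1 point:

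| Missing, active/placebo | Power at d = 0.45, last visit weeks 1–4 | Power at d = 0.45, last visit weeks 1–8 | One-sided false efficacy, no true effect |
|---|---|---|---|
| none | 84% | 83% | nominal |
| 15%/15% | 71% | 73% | nominal |
| 20%/10% | 48% | 57% | about 1% |
| 10%/20% | 87% | 85% | about 6% to 7% |

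The level to compare with is one-sided 0.025 (Interim analysis). Over repeated runs, power in the 20%/10% row lay between about 47% and 58%.

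**When drop-out depends on the current score.** With worse scores leaving more often during titration, LOCF gave −0.41 (14%/15%), −0.27 (19%/10%) and −0.55 (9%/20%) at a true −0.45. A likelihood analysis of all visits gave −0.449, −0.444 and −0.452. That data model is missing-at-random, so it favours the likelihood method by construction. It shows only that the scheduled scores hold the information that LOCF discards.

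**If fewer scores are missing.** Suppose half of the non-completers still attend Visit 8, so 7.5% are missing on average. With f = 0.25, a 10%/5% split gives −0.45 × 0.925 + 0.75 × 0.05 = −0.379, and 5%/10% gives −0.45 × 0.9625 − 0.0375 = −0.471. The pattern is the same and the departure from 0.45 is smaller.

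**The case against.** Several limits on the point stand.

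- **Only some missing scores are affected by titration.** The last permitted step is day 19, so the Visit 5 rating already follows it, and Visits 6 and 7 are in the maintenance period. Drop-outs last seen at about Visits 2 to 4 are the problem.
- **15% non-completers is not 15% missing week-10 scores.** Patients who stop drug stay on schedule, and an observed week-10 score is used as it is.
- **The planned checks are not empty.** Additional analyses states that they are meant to assess the imputation method, and a complete-case ANCOVA does drop the no-change assumption. But it ignores the intermediate scores, and neither comparison varies what is assumed about unobserved outcomes. It is a limited check.
- **The trial is labelled exploratory phase II.** The primary analysis is nevertheless called confirmatory.

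A reader might also infer more than the documents support.

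- **LOCF works against dronabinol.** More or earlier drop-out on active is not documented. The Safety section calls dronabinol well tolerated in general, with adverse reactions limiting the individual dose, and each titration step is optional. Either direction remains possible.
- **20%/10% drop-out inflates the type I error.** Its two-sided error is about 8%, but about 7% of that lies in the harm direction. False efficacy is below 0.025. The inflation that matters for the one-sided test comes from the reverse pattern.
- **LOCF causes the whole fall from 80% power.** Under equal drop-out, a comparison of the two methods gave 74% for LOCF and 75% for a likelihood analysis, which simulation error cannot separate. With no recovery of information at all (67 per arm), power would be 0.734. Most of that loss comes from missingness itself.
- **The full analysis set cannot be analysed, or the responder and remitter endpoints are undefined.** The article gives no rule for treated patients without any post-baseline score. Secondary analyses says "For all other secondary endpoints, no imputation is planned" after applying the primary rule to the primary score at other times. The full protocol and interim analysis plan are in supplements not shown, and may settle these details.

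**Conclusion.** The point holds as a should-fix. The article states a specific rule for the confirmatory analysis, so this is not a detail left to another document. The rule's no-change assumption conflicts with the titration design for patients last rated at about Visits 2 to 4.

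The size is conditional. With 15% missing on average and linear improvement in both arms, the estimate of a true 0.45 ranges from about 0.31 to about 0.49 as the imbalance in drop-out changes sign. It widens to about 0.27 to 0.55 if patients with worse scores leave more often. With fewer missing scores, equal drop-out or little improvement on placebo, the distortion is smaller. Under equal drop-out with no true effect there is no bias. The case for change is that the rule's performance depends on a drop-out pattern nobody can know in advance, while a better-supported analysis needs no additional data.

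**What to change.** Keep the baseline- and centre-adjusted comparison at week 10 in the full analysis set. Replace LOCF with one of the following:

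- multiple imputation by arm, using B2 at baseline and weeks 1, 2, 3, 4, 6 and 8, including values observed after study drug was stopped; or
- an MMRM on the same visits, with the week-10 contrast as the primary estimate.

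Use the same rule at the interim analysis. Both options assume missing-at-random, so add a reference-based or tipping-point sensitivity analysis that makes unobserved week-10 scores progressively worse in the active arm. LOCF can remain as a supportive analysis at most.

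Also reconcile the B2 visits: Table 2 includes Visit 2, while the secondary endpoint list covers Visits 3 to 7.

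The cost is amended wording in the protocol and analysis plan, plus some programming, ideally before any unblinded look. The standard error will be slightly larger than under LOCF (about 3% in a simulation with equal drop-out). No new data or visits are needed.
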